## Abstract

Different musculoskeletal conditions affect people all over the world and were considered by the WHO to be the main cause of disability in 4 of 6 regions in 2017, with an increase in the associated burden and the impact they have on today's society. One of these conditions is related to the knee, which is associated with complex and vulnerable injuries associated with ligaments, menisci, and cartilage. After surgery, there is a reflex inhibition of motor neurons and immobilization, there is rapid atrophy and weakness in the different associated muscles, affecting proprioception, strength and muscle function, compromising quality of life. The aim of this article is to describe a protocol for a rehabilitation program after surgery for people with knee injuries. An experimental study will be carried out with 75 patients, with control and experimental groups. In both groups, initial measurements will be compared with measurements after the program, at different times. It is hoped that this study will generate significant information on rehabilitation intervention for people with knee injuries.

Specifications table

**Table utbl0001:** 

Subject area:	Medicine and Dentistry
More specific subject area:	Rehabilitation; Health policies and research in health services.
Name of your protocol:	PROM_R
Reagents/tools:	EQ-5D-5L - EuroQol 5 Dimensions HADS - Hospital Anxiety and Depression Scale BREQ2 - Behavioural Regulations in Exercise Questionnaire
Experimental design:	An experimental study with 75 selected participants. Protocol that includes rehabilitation intervention in adults with an experimental group and a control group, enrolled in rehabilitation institutions located in rural and urban regions, carried out by the physiotherapist. Performance at the beginning of the program will be measured and then compared with performance after the supervised intervention in both groups. Participants will be included in the intervention after agreeing to take part in the study.
Trial registration:	Study protocol was registered in Clinicaltrials.gov with the number NCT06206018.
Ethics:	The study protocol was submitted to the Ethics Committee of the Nacional School of Public Health – NOVA University of Lisbon and was approved (CEENSP n°3/2022).
Value of the Protocol:	- The protocol is important for evaluating the effects of a structured four-week rehabilitation program on the quality of life reported by participants after knee injury, and who live in rural or urban regions. - There is a lack of knowledge about the selection of Patient-Reported Outcomes Measures (PROMs) considering the different domains envisaged by patients with knee pathology when participating in rehabilitation programs. - This article will contribute recommendations for a rehabilitation program based on supervised physical exercise after knee injury.

## Description of protocol

Different musculoskeletal conditions affect people all over the world and were considered by the WHO to be the main cause of disability in 4 of its 6 regions; they cause an increase in the associated burden with a real impact on our society. One of these conditions is related to the knee, which is associated with complex and vulnerable injuries, the most common of which are caused by ligaments, menisci, and cartilage. Structured rehabilitation programs are essential as they improve quality of life by optimizing proprioception, strength, and muscle function, which can be compromised immediately after surgery as a consequence of reflex inhibition of motor neurons and immobilization [1].

The aim of this experimental clinical study is to analyze the effects of a 4-week supervised rehabilitation program on the quality of life reported by participants after knee surgery. As a secondary objective, we intend to analyze the impact that the program has on the level of anxiety and motivation to practice exercise through the application of PROMs, in patients who have undergone knee surgery.

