### Procedures

Participants will complete the intervention described in Table 1, based on the updated Journal of Orthopaedic and Sports Physical Therapy (JOSPT) guidelines for knee injuries [3].

**Table 1 tbl0001:** Knee treatment intervention protocol.

Interventions	week			
	1	2	3	4
Massage	x	x	x	x
Passive Mobilization	x	x		
Active Mobilization	x	x	x	x
Neuromuscular Electrical Stimulation (NMES)	x	x	x	x
Proprioceptive Training		x	x	x
Isometric Exercises: Quadriceps; Vastus Medialis Oblique Muscle (VMO); Hip Adduction	x	x		
Isotonic Exercises: Gastrocnemius	x	x		
Isotonic Exercises: Quadriceps; Hip extension; Hip adduction; Hip abduction; Hamstrings	x	x	x	x
Standing Isotonic Gastrocnemius Exercises		x	x	x
Wall Slide 0° to 30°		x		
Wall Slide 0° to 45°			x	
Wall Slide 0° to 90°				x
Static Ergometer		x	x	x
Treadmill Progression: gait>run				x
Single Leg Vertical Jump				x
Specific Sport Exercises				x
Lower Limbs Stretching	x	x	x	x
Cryotherapy	x	x		

Initial data will be collected at baseline (T0), the intervention will then take place, an evaluation will be carried out shortly after the end of the intervention (T1) and the final evaluation will be carried out 6 months after the end of the intervention (T2). The following PROMs will be applied before and after the intervention:-The “**EQ-5D-5L**” instrument comprises five dimensions, each describing a different aspect of health: Mobility, Self-care, Usual activities, Pain/discomfort, and Anxiety/depression. Each dimension has five response levels: no problems, slight problems, moderate problems, severe problems, unable to/extreme problems. The visual analogue scale of this questionnaire has a score of 0–100. Higher scores mean better quality of life and lower scores indicate lower quality of life [4];-The “**HADS**” instrument, developed to detect symptoms of anxiety and depression, is made of 14 items, subdivided into two subscales - Anxiety and Depression, with a maximum score of 21 points for each subscale. The subscale scores can be calculated separately or together, with each item scored from 0 (absent) to 3 (extremely present) [5];-The “**BREQ2**” instrument has 19 items with five response options on a Likert scale, where 0 is "not true for me" and 4 is "often true for me" to assess the constructs of: amotivation, external regulation, introjected, identified and intrinsic motivation. The results can vary from 24 (lowest self-determination) to 20 (highest self-determination) [6].

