## Statistical methods

The Statistical Package for Social Sciences (SPSS®) 29 software (IBM Corp, Armonk, New York, USA) will be used. Different statistical procedures will be used to analyze the data, including descriptive and inferential techniques. Non-parametric tests, Chi-square and Mann-Whitney U will be used when the normality of the distribution is not verified. If normality or small deviations allow the use of parametric tests, we will apply the Student's *t*-test for independent measures.

The differences between the groups at the different assessment times will be calculated using a two-factor ANOVA. A Multiple Linear Regression will be carried out with each dependent variable and the intervention to analyze its effect on the different outcomes found. For the statistical tests, a 95 % confidence level will be considered, even if the p-values do not indicate a significant difference, we will report the effect size to give meaning and emphasize the power of the results [10].

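### Quality of life is the main objective, but no EQ-5D-5L score or visit is named primary, so the 5% error rate does not attach to the main conclusion

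*Protocol article*

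**What the plan says.** Under Description of protocol, the aim is to "analyze the effects of a 4-week supervised rehabilitation program on the quality of life reported by participants after knee surgery". Anxiety and motivation to exercise form a secondary objective.

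Under Procedures, the EQ-5D-5L "instrument comprises five dimensions, each describing a different aspect of health: Mobility, Self-care, Usual activities, Pain/discomfort, and Anxiety/depression". The same paragraph adds: "The visual analogue scale of this questionnaire has a score of 0–100". No index value is mentioned. Assessments are at baseline (T0), shortly after the intervention ends (T1) and 6 months after it ends (T2). The Evaluation section repeats these three visits.

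Under Sample size calculation, the inputs are alpha 0.05, power 0.5 and effect size 0.5, giving at least 60 patients, raised to 75 for a 20% loss. The effect size is attached to no outcome. The 6-month evaluation appears there only as a reason for the loss allowance.

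Under Statistical methods: "The differences between the groups at the different assessment times will be calculated using a two-factor ANOVA". A multiple linear regression is also to be carried out "with each dependent variable and the intervention to analyze its effect on the different outcomes found". On the level: "For the statistical tests, a 95 % confidence level will be considered". No result is singled out as the one that answers the main objective.

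**The concern.** The article ranks its objectives but stops one step short: the leading objective remains a concept. Six EQ-5D-5L scores are described and there are two post-baseline visits, so up to twelve score-by-visit comparisons could each be reported as an effect on quality of life. A reader of the final paper could not tell whether the result put forward was chosen before or after the data were seen.

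The sample size is affected too. An effect size of 0.5 has a definite meaning only for a particular score at a particular visit. Without these, neither the alpha nor the power in the calculation belongs to an identifiable test.

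**Working it through.** **Inputs from the protocol article.** Five dimensions and one VAS (Procedures); two post-baseline visits (Procedures, Evaluation); 0.05 per test (Statistical methods, Sample size calculation); effect size 0.5, power 0.5, minimum 60, loss 20%, total 75 (Sample size calculation).

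**Inputs that are assumptions.** The number of quality-of-life tests and the correlation between their test statistics. Neither is stated, so both are varied. All tests are taken as two-sided.

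**1. The plan's own figure.** For two equal groups and a two-sided test, the normal approximation is n per arm = 2 × (z for alpha + z for power)² / d². With power 0.5 the second z is 0, so n = 2 × (1.960 + 0)² / 0.5² = 2 × 3.841 / 0.25 = 30.7, rounded up to 31 per arm or 62 in total. This is close to 60. The exact t calculation gives 64, and a one-sided test gives 44 to 46. The loss allowance checks: 60 / (1 − 0.20) = 75. So the figure is consistent with a single two-sided comparison of two means at 0.05, that is, with one test of one score at one time.

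**2. Independent tests.** With k tests at 0.05 and no true effect, the chance of at least one significant result is 1 − 0.95^k.

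- k = 2 (one score, two visits): 1 − 0.9025 = 9.8%
- k = 6 (six scores, one test each): 1 − 0.7351 = 26.5%
- k = 12 (six scores, two visits): 1 − 0.5404 = 46.0%

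**3. Correlated tests.** EQ-5D-5L scores from the same patient are related, and so are the two visits. With a common correlation between all pairs of normal test statistics, the same probability is:

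| Tests assumed | 0 | 0.3 | 0.5 | 0.7 |
|---|---|---|---|---|
| 2 | 9.8% | 9.5% | 9.1% | 8.3% |
| 6 | 26.5% | 24.1% | 20.7% | 16.4% |
| 12 | 46.0% | 39.7% | 31.9% | 23.2% |

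If the correlation between scores and the correlation between visits are instead set separately and multiplied for pairs that differ in both, the twelve-test range is 26–46%, and about 35% with both at 0.5.

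**4. After the fix.** One score at one visit, tested once: 5%. If all twelve comparisons were kept as alternative routes to success, Bonferroni would require 0.05 / 12 = 0.0042 for each.

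**The case against.** **The size of the inflation is not in the document.** A reader might infer that the false-positive chance is one in three or higher. The article does not support that as a lower bound. It lists the five dimensions to describe the questionnaire and does not say that each will be tested. The two-factor ANOVA could yield one group-by-time test per score rather than one per visit. One in three needs about twelve moderately correlated tests, or at least eight independent ones (1 − 0.95^8 = 33.7%). This objection stands, and the result has to be given as a range.

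**The several procedures are not several independent chances.** It is tempting to count the t-test, Mann-Whitney, ANOVA and regression as multiplying the tests. But the t-test and Mann-Whitney are alternatives chosen on normality, and the reference to each dependent variable belongs to the regression sentence only. ANOVA and regression on the same data are highly correlated and would add only modestly. This also stands, and the procedures are left out of the calculation.

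**The objectives are already ordered.** Anxiety and motivation are secondary as written, so HADS anxiety and BREQ2 do not add to the error on the main question. This stands. It does not settle which quality-of-life result is primary.

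**This is a condensed article and the analysis plan is not shown.** Multiplicity adjustment and testing order, especially for secondary outcomes, may well be in that plan, and their absence here is no defect. The primary score and visit are different. They define the question and the sample size, and a protocol that gives objectives, instruments, visits, sizing and tests would be expected to connect them.

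**The sizing does not point to a visit.** A reader might infer from the Sample size calculation that the trial was sized for T2. Only the loss allowance is linked to 6 months, not the effect size. T1, directly after the programme, is an equally possible reading of the aim.

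**Conclusion.** The point holds in a limited form. The article names quality of life as its main objective, names no EQ-5D-5L score or visit as primary, ties its effect size to no outcome, and applies 95% confidence to the tests. If any significant quality-of-life result counts as success, the false-positive chance on the main question exceeds the 0.05 used for sizing in every scenario with more than one eligible test.

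The amount depends on assumptions about test count and correlation (0 to 0.7): about 8–10% for one score at two visits, about 16–26% for six scores tested once each, and about 23–46% for six scores at both visits, where moderate correlation gives about one in three. The width of that range reflects how much has been left open. The data would remain usable, so this should be corrected, but it does not invalidate the trial.

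**What to change.** Before any outcome data are seen, name in the protocol one primary score, one primary visit and one between-group test at two-sided 0.05, and state that the effect size of 0.5 refers to that comparison.

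A suitable choice is the EQ-5D-5L VAS at T2. The VAS is the only overall EQ-5D score that the article describes, and T2 is the visit behind the 20% loss allowance. The comparison can use the planned multiple linear regression with the T0 value added as a covariate. No baseline covariate is stated at present, so this is an addition to the plan. Another score or visit would cure the defect equally well, provided the sponsor fixes it in advance.

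Treat the other visit and the five dimensions as secondary, alongside HADS and BREQ2. Report them as estimates with confidence intervals and no claim of significance, or with Holm adjustment. HADS depression, which the stated objectives do not mention, should be placed there explicitly.

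The cost is protocol wording, with no extra patients, visits or questionnaires. The registry record was not available, so whether its wording must change cannot be said here, but the two should agree. The real downside is that a favourable secondary result could no longer carry the main conclusion.

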### Study design

An experimental study will be carried out, following the recommendations of CONSORT (Consolidated Standards of Reporting Trials) to assess the effectiveness of the intervention [2].

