### Subjects

Participants will be selected from among patients with knee pathology who have undergone surgery, following a physiotherapy appointment.

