### Sample size calculation

GPower@ software was used to calculate the sample size, determining a minimum of 60 patients assuming an alpha error of 0.05, a sample power of 0,5 (Power = 1-β err prob), and an effect size of 0,5. Anticipating a potential loss of 20% in follow-up due to the period required for the program (with evaluation at 6 months) and based on the numbers from each of the centers, a total of 75 patients will be recruited.

The experimental group will complete the rehabilitation program, in which the intervention takes place in five sessions per week over 4 weeks, with the physiotherapist supervising all the sessions (Fig. 1).

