### Recruitment

Participants will be recruited from rehabilitation clinics in an urban region (Oeiras-Portugal) and a rural region (Portel-Portugal), where they have started a recovery program. They will be invited to take part in the study immediately after their physiotherapist appointment, will be informed about the aims of the study and asked for informed consent (already approved by the Ethics Committee of the National School of Public Health - NOVA University of Lisbon).

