### Intervention description

The standard intervention is based on the physiotherapy clinical practice guidelines, updated by the JOSPT for knee injuries, which include lower limb massage, mobilization, neuromuscular strengthening and rehabilitation, teachings, quadriceps neuromuscular electrical stimulation and cryotherapy [3]. The intervention group will complete the four-week rehabilitation program, with five sessions per week, performed and supervised by the physiotherapist. All patients follow the same order of treatment and exercises, starting with massage and mobilization, followed by the corresponding exercise program, and ending with Neuromuscular Electrical Stimulation (NMES) and cryotherapy (Table 1). This four-week intervention for rehabilitation of the knee joint after surgery makes it possible to improve passive and active knee extension (knee extension range of motion), increase quadriceps strength, improve gait performance, and optimize the patient's functionality. The control group will follow a standard six-week rehabilitation program.

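### The article claims an experimental effectiveness study under CONSORT but states no method of assigning patients to the four- or six-week group, and names no centre factor or baseline covariate

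*Protocol article*

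**What the plan says.** Study design in the protocol article reads "An experimental study will be carried out, following the recommendations of CONSORT" and gives assessing effectiveness as the purpose.

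The Specifications table describes the arms: "Protocol that includes rehabilitation intervention in adults with an experimental group and a control group, enrolled in rehabilitation institutions located in rural and urban regions". Intervention description gives the experimental group four weeks of supervised sessions and adds: "The control group will follow a standard six-week rehabilitation program".

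Entry to the study is described in three places:
- Subjects: "Participants will be selected from among patients with knee pathology who have undergone surgery, following a physiotherapy appointment".
- Recruitment: "Participants will be recruited from rehabilitation clinics in an urban region (Oeiras-Portugal) and a rural region (Portel-Portugal), where they have started a recovery program". Invitation, information and consent follow.
- Specifications table: "Participants will be included in the intervention after agreeing to take part in the study".

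None of these sections mentions randomisation, a sequence, concealment, stratification, an allocation ratio or a non-random assignment rule.

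Statistical methods lists a t-test or Mann-Whitney and Chi-square tests, a two-factor ANOVA of group differences across assessment times, and a multiple linear regression of each outcome on the intervention. T0, T1 and T2 are the assessment times (Procedures, Evaluation). Centre or region appears in no test or model, and the intervention is the only regression predictor named.

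**The concern.** How the arms are formed decides what a comparison of the arms can show. With random assignment, a difference at T1 or T2 can be attributed to the programme, apart from chance. Without it, the same difference also carries whatever else distinguishes the two groups.

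Several such differences are plausible here. Inclusion and exclusion criteria admit any adult after knee surgery and set no limit on the type of operation or the time since it, apart from excluding earlier surgery on the same knee. Recruitment spans an urban and a rural region, and Sample size calculation bases the total partly on the numbers from each centre. Motivation to exercise is itself a secondary outcome, so an assignment rule related to motivation would bias that outcome directly.

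The analysis offers limited protection, since it names no centre or region term and no baseline covariate. At stake is whether the study can support the effectiveness conclusion for which it is set up.

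**Working it through.** **1. The plan's own figures.** Sample size calculation gives "determining a minimum of 60 patients assuming an alpha error of 0.05, a sample power of 0,5 (Power = 1-β err prob), and an effect size"; the value entered there is 0.5. Loss is put at 20% and 75 are recruited. Sidedness, test and allocation ratio are not stated. Assume a two-sided, 1:1 comparison of two means with 0.5 in SD units.
- Per arm: 2 × (1.96 + 0)² / 0.5² = 30.7, rounded up to 31. The total is 62, against 60 stated.
- Recruited: 60 / (1 − 0.20) = 75, which is exact.

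The figures are close to what a two-arm comparison would give, but they do not show how the arms are formed. The planning power of 0.5 is a separate matter.

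**2. The assignment step.** Read in order, the article gives an appointment, an invitation, consent, T0, then four weeks for one group and six for the other. Between consent and programme there is no step that sends a patient to one group.

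**3. Where baseline enters the analysis.** T0 is one of the assessment times, so it enters the two-factor ANOVA as a level of time. A group-by-time contrast then compares change from T0. T0 is not named as a covariate in the regression, and no use of it is stated for the t-test or Mann-Whitney comparison.

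**4. Illustration: imbalance in starting score.** Assumed, not from the article: the experimental group starts d = 0.3 SD higher, the T0–follow-up correlation is r = 0.5, SDs are equal at both times, and there is no true programme effect.
- Unadjusted follow-up difference: bias = r × d = 0.5 × 0.3 = +0.15 SD.
- Change from T0: bias = r × d − d = 0.15 − 0.30 = −0.15 SD.
- Relative to the planned effect: 0.15 / 0.5 = 30%, in opposite directions.

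Over the range r = 0 to 1 with d = 0.3, the follow-up bias runs from 0 to +0.30 SD and the change bias from −0.30 to 0.

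Using T0 as a covariate removes the bias in this model. It would not do so if the two groups differed in a lasting way. If the whole 0.3 SD gap persisted to follow-up, adjustment with slope 0.5 would leave 0.30 − 0.5 × 0.30 = +0.15 SD. Adjustment therefore does not replace randomisation.

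**5. Illustration: imbalance in region.** Assumed: 30 per arm, two-sided 5% test, no true effect, an urban–rural difference of D SD, and arms that differ in urban share by q. Then bias b = D × q, SE = √(2/30) = 0.258, and the false-positive rate is 1 − Φ(1.96 − b/SE) + Φ(−1.96 − b/SE).

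| D (SD) | q = 0 | q = 0.25 | q = 0.50 | q = 1.00 |
|---|---|---|---|---|
| 0.2 | 5.0% | 5.4% | 6.7% | 12.1% |
| 0.5 | 5.0% | 7.7% | 16.2% | 49.1% |

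For q below 1, a region term can separate the two effects. At q = 1, group and region are the same variable and no model term can separate them.

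**The case against.** The strongest defence is that the document is a condensed article. An experimental study tied to CONSORT may well be randomised, and lists of covariates commonly sit in an analysis plan that is not shown. For covariates this has some force: the word multiple in the regression implies predictors beyond the intervention. For the assignment method it does not suffice, because that is core design content. The article has room for a week-by-week treatment table, yet none of its design, recruitment or procedure sections covers assignment.

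Some stronger readings are tempting, and the text does not support them:
- **That patients are not randomised.** The article is silent, and silence shows only that the method is not stated.
- **That there is one clinic per region, or that each group belongs to one region.** Recruitment speaks of clinics in the plural and gives no number per region. The Specifications table can be read as both groups being enrolled in both regions.
- **That patients choose their group.** The sentence "Participants will be included in the intervention after agreeing to take part in the study" follows one about both groups and is most naturally about consent. Nothing states assignment by preference, therapist or existing care.
- **That baseline is ignored.** It enters the ANOVA as a time level.
- **That the plan carries a 30% bias.** The 0.15 SD rests on assumed inputs, and the +0.15 applies only to an unadjusted follow-up comparison, which the article does not name as primary.

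**Conclusion.** The point holds in this form: the article claims to assess effectiveness in an experimental study, states no method of assigning patients to the two groups, and names no centre or region factor and no baseline covariate beyond T0 as a time level. As written, the design does not support the effectiveness claim.

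The article gives no figure from which the size of any bias could be derived. On the assumed starting imbalance the bias is +0.15 or −0.15 SD, depending on the contrast, against a planned effect of 0.5. On the assumed regional differences the false-positive rate ranges from 5.0% with balanced arms to 49.1% when a 0.5 SD regional difference coincides with group. These values show sensitivity to the unstated assignment rule and do not predict what will happen. If patients are in fact randomised within centre, the main defect is one of reporting and the remaining gap is the unnamed centre and T0 terms.

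**What to change.** State and use 1:1 randomisation within each centre from a concealed list, with the group assigned after T0 is completed. Include centre and the T0 score as covariates in the regression of the T1 and T2 outcomes.

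If groups are formed any other way:
- call the study non-randomised and name the allocation rule;
- make sure both groups are recruited in each centre;
- adjust for centre and T0 score, and for type of surgery and time since surgery if these are recorded (the article does not mention collecting them);
- restrict the conclusion to association.

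The randomised option costs an allocation list and a few degrees of freedom with about 60 evaluable patients. The T0 score is already collected, so no extra patients or visits are needed. The non-randomised option uses more degrees of freedom and may need two extra baseline items. The decision has to precede enrolment, because assignment cannot be repaired afterwards.
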